# Study of negative pressure wound therapy as an adjunct treatment for acute burns in children (SONATA in C): protocol for a randomised controlled trial

**DOI:** 10.1186/s13063-019-3223-9

**Published:** 2019-02-13

**Keywords:** Paediatric, Burns, Negative-pressure Wound Therapy, Re-epithelialisation, Pain, Burn wound progression, Itch, Randomised controlled trial

## Abstract

**Background:**

Although negative pressure wound therapy (NPWT) is widely used in the management of several wound types, its efficacy as a primary therapy for acute burns has not yet been adequately investigated, with research in the paediatric population particularly lacking. There is limited evidence, however, that NPWT might benefit children with burns, amongst whom scar formation, wound progression and pain continue to present major management challenges. The purpose of this trial is to determine whether NPWT in conjunction with standard therapy accelerates healing, reduces wound progression and decreases pain more effectively than standard treatment alone.

**Methods/design:**

A total of 104 children will be recruited for this trial. To be eligible, candidates must be under 17 years of age and present to the participating children’s hospital within 7 days of their injury with a thermal burn covering <5% of their total body surface area. Facial and trivial burns will be excluded. Following a randomised controlled parallel design, participants will be allocated to either an active control or intervention group. The former will receive standard therapy consisting of Acticoat™ and Mepitel™. The intervention arm will be treated with silver-impregnated dressings in addition to NPWT via the RENASYS TOUCH™ vacuum pump. Participants’ dressings will be changed every 3 to 5 days until their wounds are fully re-epithelialised. Time to re-epithelialisation will be studied as the primary outcome. Secondary outcomes will include pain, pruritus, wound progression, health-care-resource use (and costs), ease of management, treatment satisfaction and adverse events. Wound fluid collected during NPWT will also be analysed to generate a proteomic profile of the burn microenvironment.

**Discussion:**

The study will be the first randomised controlled trial to explore the clinical effects of NPWT on paediatric burns, with the aim of determining whether the therapy warrants implementation as an adjunct to standard burns management.

**Trial registration:**

Australian New Zealand Clinical Trials Registry, ACTRN12618000256279. Registered on 16 February 2018.

**Electronic supplementary material:**

The online version of this article (10.1186/s13063-019-3223-9) contains supplementary material, which is available to authorized users.

## Background

The acute burn wound is a complex, dynamic injury that presents a range of challenges for patients and clinicians alike. It has been described as “the ultimate inflammatory injury” [1] and “amongst … the most devastating afflictions on the human body” [2]. Thanks to improvements in the management of severe burns, as well as public health and infrastructural advances [3], mortality due to burns has dropped substantially in the past half century [4]. Current American and Australian in-hospital death rates stand at 3% and 2%, respectively [5, 6]. Yet burns remain one of the most common types of trauma [4, 7], particularly in children, whose developing psychomotor skills, poor spatial awareness and exploratory behaviour place them at increased risk of injury [8].

In the US and Australia, children constitute more than one third of all burns-related hospital admissions [5, 6]. Admissions, however, capture only a small percentage of the true magnitude of burn injuries in children, as between 87% and 93% of paediatric burns are treated exclusively as outpatients [9, 10]. This is attributable, in large part, to the exceeding rarity of severe life-threatening burns in high-income countries. At one of Australia’s largest tertiary paediatric burns centres, over 62% of patients present with wounds covering less than 1% of their total body surface area (TBSA), and more than 90% of all burns are thermal in origin (i.e., scalds, contact burns, flame burns or radiant heat burns) [9]. The predominant focus in modern paediatric burns care, therefore, is no longer the treatment of severe burns and their life-threatening systemic effects, but rather the improvement of functional and cosmetic outcomes in small-to-medium-sized thermal wounds.

In recent decades, the acute management of such injuries has been advanced by innovations such as early excision and grafting [11–14], skin substitute technologies [15–18] and silver-impregnated dressings [19]. Nevertheless, complications including scar formation [20], contractures [21] and pain [22] still commonly affect children who have sustained burns. In particular, hypertrophic scarring, which is defined as the formation of raised scars within the boundaries of a wound, occurs in high proportions of burns patients (with a reported prevalence ranging from 32% to 72%) [23]. For children especially, the long-term physical and psychological consequences of these scars can be devastating [24]. In addition to their effects on appearance, self-esteem and social acceptance [25–28], they can lead to contractures that impair the range of motion and function as a child grows, necessitating recurrent surgical operations to release the scar tissue [21].

The facilitation of wound closure represents one of the central aims of acute burns treatment. Prompt wound closure is essential for the prevention of scarring, as there has long been a well-understood relationship between time to re-epithelialisation and scar formation. A widely held model that was first described by Deitch et al*.* [29] and later supported by others [30, 31] identified the 3-week mark as the critical time point in the healing process with regard to scarring. Burns that fully re-epithelialise before this point have a low risk of developing hypertrophic scars (and an especially low risk if healed within 2 weeks), whilst those requiring greater than 3 weeks are highly likely to scar. Although more recent research has somewhat challenged this doctrine by finding lower rates of scarring amongst the latter group than previously reported [32]—a change some authors attribute anecdotally to the increasing use of silver-impregnated dressings [31]—burns clinicians still overwhelmingly agree that prolonged healing is a major predictor for scar formation and regard any methods aimed at accelerating re-epithelisation as worthy of consideration.

Time to re-epithelialisation is closely tied to burn depth, of which there are four broad classifications [33]. In superficial burns, only the epidermal layer of the skin is affected. Superficial partial-thickness and deep dermal partial-thickness burns extend to the papillary and reticular layers of the dermis, respectively. Burns involving the entirety of both the epidermis and dermis are categorised as full- thickness. Superficial partial-thickness burns tend to heal spontaneously within 2 weeks, whilst deep dermal partial-thickness burns exhibit more prolonged healing, typically taking 3 to 5 weeks to fully re-epithelialise. Spontaneous wound closure is impossible for full-thickness burns, which heal exclusively at the margins by scarring. The delay or inhibition of the healing process in deeper burns stems in large part from the destruction of adnexal structures in the reticular dermis. These structures, which include hair follicles, sebaceous glands and sweat glands, serve as reservoirs of keratinocytes, which can repopulate zones of cellular damage [34]. Since deeper burns are associated with significant scarring [29], they are almost always treated with debridement and grafting [35].

Burns are dynamic injuries that are vulnerable to significant changes in size, depth and severity due to a process known as burn wound conversion. This phenomenon is best understood by reviewing Jackson’s burn wound model [36], which holds that thermal injuries are characterised locally by three concentric zones. The core zone of coagulation contains irreversibly destroyed necrotic tissue. By contrast, the outermost zone of hyperaemia is marked by increased blood flow and inflammation but will invariably recover. It is within the intermediate zone between these two, the zone of stasis, that appropriate management is most vital. Tissue here remains at least temporarily viable, but if the burn is not adequately treated, may undergo progressive cellular damage and death that will result in recruitment into the zone of coagulation. A complex interplay of pathological mechanisms underlies this process.

The initial thermal insult results in a prolonged inflammatory reaction characterised by the accumulation of neutrophils [37, 38]. In addition to releasing harmful cytokines and reactive oxygen species associated with collagen denaturation, keratinocyte apoptosis and DNA damage [37, 39], these neutrophils adhere to the endothelial lining of local blood vessels [40], leading to vascular plugging. Leukocyte adherence, in combination with increased vascular permeability and reduced interstitial hydrostatic pressure [41, 42], also contributes to oedema formation [43], which itself significantly impairs perfusion to the burn wound. Local circulation is further compromised by microvessel thrombosis arising from a peak in hypercoagulability that occurs 2 to 3 hours following injury [44]. Finally, oxidative stress, linked with over-activity of xanthine oxidase and NADPH oxidase, damages cellular proteins, nucleic acids and lipids central to the healing process [45, 46]. Subsequent expansion of the depth and surface area of a burn can continue for up to 5 days post-injury [47]. Adequate first aid and the application of appropriate dressings may alleviate some of these factors [48], but no techniques have yet been found that definitively minimise burn wound progression [49].

Even more prevalent and difficult to prevent than scarring, pain persists as one of the greatest unmet challenges in burns management [50]. Despite the development of sophisticated analgesic protocols, unrelieved pain continues to be reported at high rates amongst burns patients, often ranking as their most frequent complaint [51]. The risks of undertreated pain are enormous: in addition to causing intense momentary suffering, anxiety and distress, it can contribute to delayed healing [52] and the development of long-term sensory disturbances [53–55], chronic pain [50] and debilitating psychological issues [56, 57]. Notably, the highest levels of pain intensity and undertreatment are associated with procedural pain resulting from dressing changes and other interventions [58–60].

A number of alternative or adjunct therapies have been proposed to help facilitate the healing process, decrease burn wound progression and minimise pain [47]. One promising approach is negative pressure wound therapy (NPWT), a technique that involves the use of a vacuum device to establish subatmospheric pressures through occlusive dressings over a wound site [61, 62]. Also known as vacuum-assisted closure, topical negative pressure, subatmospheric pressure and reticulated open cell foam therapy [63], NPWT shares the same basic principles as other medical therapies that have been in use for well over a century [64–66], but the current form of the technology, characterised by the maintenance of an evenly distributed vacuum through foam or gauze, first became commercially available in 1995 [67].

Since then, NPWT has become widely accepted in the world of wound management, particularly in the context of diabetic ulcers [68], open abdomens [69, 70], sternal wounds [71], open fractures [72] and haemangiomas [73]. Although the exact mechanism of action of NPWT is not yet fully understood, it is known to exert several effects on the local tissue environment. Among the most notable is a rise in extracellular pressure [74, 75]. This seemingly paradoxical trend is likely a result of tissue macrodeformation: as air is evacuated from the NPWT foam or gauze, the volume of the packing material decreases, consequently compressing the adjacent tissue. NPWT is believed to aid the healing process specifically by inducing wound contraction [76], generating microdeformational changes that stimulate cellular proliferation and neovascularisation [77–79], evacuating oedema fluid that adversely affects the local microvasculature, [80, 81] extracting toxins and bacteria [62, 82, 83], and preventing desiccation of the wound environment [63, 84].

NPWT has been employed at various stages in the management of burns, with the vast majority of the published literature focusing on its role in securing skin grafts [85–87]. Its efficacy as a primary treatment in the setting of acute burns, however, remains controversial [88]. A limited body of research has produced compelling evidence that thermal injuries managed acutely with NPWT demonstrate improved outcomes.


The sole existing study to investigate the effect of NPWT on acute burns in children is a retrospective review by Ren et al. [93]. In a cohort of 29 paediatric patients, 22 of whom were undergoing treatment for burn injuries, the therapy was believed to accelerate wound granulation and decrease the number of required dressing changes, though the study did not include a control group and quantitative data on granulation tissue formation were not provided. Additionally, the authors failed to specify several salient details regarding their use of NPWT, including how long post-burn it was initially administered, whether it was given in combination with silver dressings, and the specific gauge pressure and duration of each NPWT application. Nevertheless, the lack of adverse events, with no recorded episodes of bleeding or abnormally elevated pain, attested to the safety of NPWT in the paediatric population.

Absent from the literature, however, are any high-powered trials with appropriate outcome measures comparing NPWT to standard acute burns management. The only published randomised controlled trial (RCT) to investigate the role of subatmospheric pressure in the management of acute burns was provided courtesy of Honnegowda et al*.* [94]. In their trial involving 50 adolescents and adults with thermal burns under 40% TBSA, half of the participants were allocated to intermittent NPWT and the other half to 5% povidone iodine gauze dressings. Wound biopsies collected at days 0 and 10 were subjected to a series of histological and biochemical analyses. The results revealed that the burns that underwent NPWT exhibited a richer, more stable extracellular matrix, less oxidative stress, an environmental pH more conducive to wound healing, and better overall granulation tissue deposition, angiogenesis and cellular infiltrate.

Although this trial shed significant light on the biochemical effects of NPWT, its focus on surrogate endpoints rather than validated patient-centred outcomes limited the clinical applicability of its findings. Additionally, the comparator control group was managed with betadine dressings not traditionally considered standard treatment in most developed countries. The study was further constrained by the time points of its data collection, which would fail to capture the full duration of re-epithelialisation for the majority of non-superficial burns.

The most recent Cochrane systematic review [95] on the application of NPWT in acute thermal injury, published in 2014, listed an earlier RCT that commenced in 2004. All available information on this trial is confined to a single conference abstract with interim data [96]. In the reported patient cohort, comprising a total of 23 adults presenting with bilateral partial-thickness hand burns, the NPWT-treated hands showed significantly reduced burn size at days 3 and 5 post-burn, but no difference at day 14. However, due to missing data (with a completed study never published in full) as well as several methodological limitations, the authors of the Cochrane review deemed the study to be at high risk of bias [95].

To address this gap in the literature, a pilot study was undertaken in 2015 at a paediatric burns outpatient department (OPD). In a sample of 20 children with acute burns, half were given a combination of NPWT and silver-impregnated dressings whilst the other half received silver dressings alone. Preliminary data revealed that the NPWT group exhibited moderately faster healing and reported lower pain scores [97]. More broadly, it demonstrated that NPWT could function as a feasible and safe addition to standard acute paediatric burns management and provided strong support for the development of a larger RCT.

## Methods/design

### Hypothesis and objectives

The central aim of this trial is to investigate the efficacy of NPWT as an adjunct to standard therapy in the treatment of paediatric burns. The research will measure the effects of NPWT on time to re-epithelialisation, pain and burn wound progression, and determine whether it produces outcomes superior to those of standard therapy alone. Based on data from a pilot study, it is hypothesised that NPWT will accelerate healing and reduce levels of pain and pruritus between dressing changes. Removal and re-application of the NPWT system is not expected to cause significantly more pain than standard dressing changes. In terms of the impacts on overall costs, it is suspected that NPWT may increase resource usage and costs in the acute phase of treatment, but, by virtue of faster re-epithelialisation and reduced scar formation, curb the personnel and material costs required for long-term scar management.

### Study design

This prospective RCT will be a superiority trial involving two parallel treatment arms: active control and intervention. Participants will be monitored throughout the course of the acute phase of their management, up until the point of healing, and then examined at 3- and 6-month follow-ups to assess the long-term outcomes of their burns. The different phases of the trial, and the measurements taken at each, are summarised in the study design flowchart (Fig. 1) and the Standard Protocol Items: Recommendations for Interventional Trials (SPIRIT) figure (Fig. 2). The SPIRIT checklist is provided in Additional file 1.

**Fig. 1 Fig1:**
[figure not shown]
Study design flowchart. NPWT negative pressure wound therapy, LDI laser Doppler imaging, TBSA total body surface area, BBSIP Brisbane Burn Scar Impact Profile, POSAS Patient and Observer Scar Assessment Scale

**Fig. 2 Fig2:**
[figure not shown]
SPIRIT Figure. Schedule of enrolment, interventions, and assessments. B/w between, DC dressing change, POH point of healing, NPWT negative-pressure wound therapy, TBSA total body surface area, BBSIP Brisbane Burn Scar Impact Profile, POSAS Patient and Observer Scar Assessment Scale

### Study setting

Patient recruitment will take place at a large metropolitan children’s hospital that serves as the sole provider of quaternary paediatric burns care for a region with a population of 4.5 million people.

#### Participants

##### Eligibility criteria

All paediatric burns patients presenting to the hospital’s emergency department (ED) or burns OPD will be considered for eligibility. Children will satisfy the inclusion criteria if they are under 17 years of age, possess a thermal burn covering <5% of their TBSA and present within 7 days of their injury. Exclusion criteria include burns that are located on the face or deemed by clinicians to be trivial in nature (i.e., not in need of further treatment). The eligibility criteria are listed in Table 1.

**Table 1 Tab1:** Eligibility criteria

Inclusion criteria	Exclusion criteria
0–16 years of age TBSA < 5% Thermal burns Presentation to ED or burns OPD within 7 days of injury	Facial burns Trivial burns

*TBSA* total body surface area, *ED* emergency department, *OPD* outpatient department

##### Recruitment

All patients presenting to the ED or burns OPD with acute burns will be consecutively assessed for eligibility until the completion of recruitment. Nursing and surgical staff will identify eligible patients. In the ED, clinicians will first request permission from caregivers before inviting an investigator to approach them. If presenting to the burns OPD, potential participants will be approached only if they indicate a willingness to take part in research on an initial intake questionnaire.

An investigator will seek informed caregiver consent and child assent (for children 6 years and above) following the provision of verbal and written participant information. Once consent has been obtained, the patient will be randomised to one of the two treatment arms.

#### Interventions

Patients in the control group will receive the same standard dressings provided to all patients presenting to the burns OPD, which include a combination of Acticoat™ (Smith & Nephew, Hull, UK) and Mepitel™ (Mölnlycke Healthcare, Mikkeli, Finland), secured with Hypafix™ (BSN Medical, Hamburg, Germany). Likewise, the intervention group will first have their wounds dressed with Acticoat™ and Mepitel™. They will then additionally receive NPWT via the following protocol.

After applying the Acticoat™ and Mepitel™, clinicians will pack the burn with 10–20 layers of Kerlix™ (Medline Industries, Northfield, US). This antimicrobial gauze permits the vacuum to be distributed evenly across the entire wound site. In addition to their antimicrobial and moisturising properties, the silver-impregnated dressings will also serve as a wound contact layer, preventing encroachment of the Kerlix™ into the damaged tissue. An airtight seal will be generated via an adhesive film drape, to which tubing will be attached to connect the wound environment to a RENASYS TOUCH™ device (Smith & Nephew, Hull, UK). Suction will be set at a continuous subatmospheric pressure: 80 mmHg will be employed as the standard setting, but clinicians will be free to apply instead 40 mmHg in cases where ischaemia might be a concern (e.g., children under 1 year old with digit or extremity burns). Continuous pressures will be used in favour of intermittent cycles since past research showed that intermittent modes lead to elevated pain and the formation of undesirable granulation tissue [98]. The portability of the RENASYS TOUCH™ device, which can be carried around by children as young as 2 years of age in a custom-made pack, will allow patients to return to their everyday activities while still receiving NPWT.

All interventions will be carried out by burns clinicians with extensive experience in the application of dressings and NPWT. Following their initial presentation, participants will return to the OPD 3 to 5 days later for a change of dressings and, for those in the intervention group, a replacement of their NPWT system. To alleviate any additional pain from the removal of the adhesive drape, the clinicians replacing the NPWT apparatus will apply Niltac™ (ConvaTec, Greenlane, NZ), a silicone-based spray that can effectively dissolve the film and ease extraction. Participants will continue to present to the burns clinic every 3 to 5 days for dressing and NPWT changes until the wound is fully re-epithelialised or until grafting is required.

#### Randomisation

To accommodate the different scoring scales that will be used to assess pain, randomisation will be stratified by age into three groups: 0 to 3 years, 4 to 7 years, and 8 to 16 years. Allocation to the control arm and intervention arm of the study will occur at a 1:1 ratio. A random sequence will be generated by the trial statistician using the permuted block method with a random block size of either four or six participants. The statistician will then upload this sequence to the central randomisation module on the Research Electronic Data Capture application (REDCap; Vanderbilt University, Nashville, US). REDCap ensures allocation concealment by prohibiting investigators from viewing the sequence. Access is limited to an external administrator, who manages the server on which the module is hosted. Treatment allocations are assigned only after participants have been successfully enrolled and entered into the REDCap database. Randomisation will continue until each treatment arm has a minimum of 52 participants.

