#### Secondary outcome measures

##### Pain

Pain intensity will be assessed at various time points throughout the participants’ management. At their first clinical visit, baseline pain measures will be recorded immediately prior to and following dressing applications. The same measures will be repeated before and after dressing changes at every subsequent clinical visit until the burn is considered fully re-epithelialised.

A variety of measures and age-dependent scales will be utilised to assess pain. Nurses will provide an observational rating using the Face, Legs, Activity, Cry, Consolability (FLACC) scale, which is accepted as a valid and reliable tool for assessing trauma-related pain behaviours in preverbal children [99, 100]. Children aged 4 to 7 years will be asked to self-report their pain using the Revised Faces Pain Scale (FPS-R) and those aged 8 years and older will self-report their pain using a numerical rating scale (NRS).

There is a large volume of literature demonstrating the validity and reliability of the FPS-R in children as young as 4 years old [101, 102]. For children aged 8 years and older, both the NRS and a visual analogue scale are well-validated tools [103, 104], but several comparison studies have expressed a preference for the NRS, which is associated with higher levels of responsivity, adherence and ease of use in the assessment of pain intensity among adults [105, 106]. Furthermore, the NRS allows for greater consistency throughout the full duration of the trial, as the two skin/scar assessment scales employed at the 3- and 6-month follow-ups both include numerical pain ratings.

To supplement the above pain ratings, investigators will additionally document the type and dosage of all analgesic medications administered to patients by health professionals or parents during the days on which they present to the clinic.

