#### Data analysis

Conventional descriptive statistics will be used to describe the characteristics of the sample.

The potential effect of time to treatment, burn depth, burn TBSA, mechanism of injury, anatomical location of the burn and skin type will also be tested against primary and secondary measures in univariate analyses. Variables with *p*
< 0.1 will be included as covariates in the primary and secondary analyses. Sensitivity analyses will also be conducted without adjustment for covariates.

Generalised linear (mixed) models will be prepared to examine primary and secondary outcomes across time and between groups, with patients as random effect where analyses include repeated measures within a patient. If mixed models do not converge with patient as a random effect, robust variance estimates for cluster-correlated data will be used [128]. For outcomes with repeated measures, the fixed effects of time, group and interaction time by group will be tested. Data will be analysed as intention-to-treat (primary analysis) and on a per protocol basis (sensitivity analysis) if deviations from the protocol occur. Missing data will be handled using multiple imputation where appropriate. Significance will be set at 0.05. Statistical analyses will be performed using Stata (StataCorp LLC College Station, TX:) or SPSS (IBM Corp, Armonk, NY, USA).

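### Randomisation is stratified by age, but neither age nor the stratum is among the model covariates, so precision is lost to the extent that age predicts outcome

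*Protocol article*

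**What the plan says.** In the protocol article, the Randomisation section gives the reason for stratifying ("To accommodate the different scoring scales that will be used to assess pain") and then the rule: "randomisation will be stratified by age into three groups: 0 to 3 years, 4 to 7 years, and 8 to 16 years". It adds "Allocation to the control arm and intervention arm of the study will occur at a 1:1 ratio" and generates the sequence by the "permuted block method with a random block size of either four or six participants".

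The Data analysis section lists the variables to be screened one at a time against the outcomes: "The potential effect of time to treatment, burn depth, burn TBSA, mechanism of injury, anatomical location of the burn and skin type". Those with a p-value below 0.1 "will be included as covariates in the primary and secondary analyses". It continues: "Sensitivity analyses will also be conducted without adjustment for covariates". For repeated measures, the fixed effects to be tested are time, group and their interaction. No section says that age or the age stratum enters any model.

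The Pain section states "A variety of measures and age-dependent scales will be utilised to assess pain": a nurse-rated FLACC score, for which no age limit is set; the FPS-R by self-report at 4 to 7 years; and a numerical rating scale from 8 years. It does not say whether scores from different scales will be pooled.

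**The concern.** Permuted blocks within age strata keep the arms close to balanced on age. If age is related to the outcome, that balance lowers the true sampling variance of the treatment contrast. A model without the stratum still counts the spread between age groups as residual noise, so the standard error it reports exceeds the real one. Intervals come out wider than the design has earned, the test runs below its nominal level, and a real effect is somewhat easier to miss.

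The document gives some reason to expect age to matter for certain outcomes. It stratifies because the pain scales differ by age. Under Treatment satisfaction it reports a clinical impression that older children tolerate the therapy less well, and says it wants to see how attitudes vary with age. It gives no figure for how strongly age predicts healing time.

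**Working it through.** **Inputs from the protocol article, Sample size section:** mean healing time 12.4 days with SD 5.4; target reduction 3.4 days; 104 participants; power above 80%; drop-out up to 20%; significance level 0.05. Sidedness is not stated; two-sided is assumed.

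**Assumed, because the document gives no figure:** R², the share of outcome variance explained by age stratum (strictly, beyond the covariates entered). A linear model for days to healing is also assumed.

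**1. The plan's own figure.** A two-sample t-test with effect 3.4/5.4, two-sided 0.05 and power 0.80 needs 40.6, so 41 per arm. Then 41/(1 − 0.20) = 51.25, so 52 per arm and 104 in total. The stated figure is reproduced exactly.

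**2. Baseline precision.** The evaluable number per arm is 52 × 0.80 = 41.6. SE = 5.4 × √(2/41.6) = 1.184 days. The standardised effect is 3.4/1.184 = 2.872. Power by the normal approximation is Φ(2.872 − 1.960) = 81.9%.

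**3. Stratum omitted or included.** With 5.4 as the total SD and age balanced by design, the true SE is 1.184 × √(1 − R²), while the model without the stratum still reports about 1.184.

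- Reported SE relative to true SE: 1/√(1 − R²)
- Real two-sided level without the stratum: 2 × [1 − Φ(1.960/√(1 − R²))]
- Power without the stratum: Φ((2.872 − 1.960)/√(1 − R²))
- Power with the stratum: Φ(2.872/√(1 − R²) − 1.960)

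| Assumed R² | SE too wide by | Real level, omitted | Power, omitted | Power, included | Difference (points) |
|---|---|---|---|---|---|
| 0 | 0% | 0.050 | 81.9% | 81.9% | 0 |
| 0.05 | 2.6% | 0.044 | 82.5% | 83.8% | 1.3 |
| 0.10 | 5.4% | 0.039 | 83.2% | 85.7% | 2.5 |
| 0.20 | 11.8% | 0.028 | 84.6% | 89.4% | 4.8 |

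**4. Simulation check.** The formulas assume perfect balance within strata, which small blocks and drop-out do not quite deliver. In 5000 simulated trials per setting (blocks of 4 or 6, 20% random drop-out, assumed stratum shares of 50%, 25% and 25%), the results were:

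| Assumed R² | Null rejection, omitted | Null rejection, included | Power, omitted | Power, included |
|---|---|---|---|---|
| 0.05 | 4.9% | 5.2% | 80.7% | 81.9% |
| 0.10 | 3.9% | 5.1% | 82.0% | 84.5% |
| 0.20 | 3.6% | 5.3% | 83.2% | 89.0% |

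The direction and rough size agree. At R² = 0.20 the real level is nearer 0.05 than the formula says.

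**5. Pain.** The document gives no SD, target effect or relation to age for pain, so no figure can be computed. The formula in step 3 also does not carry over directly to repeated measures: with a patient random effect, stable age differences go mainly to that effect, and the time-by-group term is largely a within-patient contrast.

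**The case against.** The strongest objection is one of scope. This is a journal article, the statistical analysis plan is not shown, and naming the stratification factor in the model is often left to that plan. The article does not call its covariate list exhaustive and does not exclude age. So it would go too far to say that age can never enter a model. But the article is not silent either: it names a covariate set, an entry rule and the repeated-measures fixed effects, and a plan written to that text would leave the stratum out.

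A second objection is that the size is unknown. The article ties healing time closely to burn depth, which is already a candidate covariate, so what counts is what age adds after depth and the others. That stands. It makes the loss conditional and possibly small.

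Three stronger readings are tempting and are not supported:

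- **That the trial becomes underpowered.** If the age-adjusted test is fixed at exactly 80%, then Φ(2.80 − 1.96/√(1 − R²)) gives 77% at R² = 0.10 and 73% at 0.20 without adjustment. That treats 5.4 days as the spread within age groups. The article presents it as the SD reported with standard therapy and mentions no age adjustment. Taken as the total SD, it leaves unadjusted power above 80%.
- **That omission at R² = 0.20 amounts to discarding a fifth of the sample.** That describes interval width. Even the 73% figure corresponds to (2.57/2.80)² = 0.84 of the sample, a loss of about 16%.
- **That pain suffers most.** This needs scores from different scales to be pooled, which the article never says. Analysed scale by scale, the FPS-R (4 to 7 years) and the numerical scale (8 years and over) each sit within one stratum and lose nothing. FLACC would span all three strata if used at every age, but its age range is not fixed.

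**Conclusion.** The point holds as a free improvement. The plan stratifies randomisation by age and, as written, analyses without it. If age predicts an outcome beyond the entered covariates, intervals will be too wide and tests conservative. The error creates neither bias nor false positives.

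For the primary outcome the cost is modest: roughly 1 to 5 points of power against the age-adjusted model for R² between 0.05 and 0.20, and none at R² = 0. This rests on assumed values of R², on 5.4 days being the total SD, on a two-sided test and on a linear model. The planned power is met either way, and the sample size needs no change. For pain, the direction depends on whether scales are pooled and the size cannot be stated.

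**What to change.** Add to Data analysis: the three-level age stratum used in randomisation is a fixed covariate in the primary model, and in every secondary model that spans more than one age stratum, regardless of its univariate p-value.

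The restriction is needed because the stratum is constant, and cannot be fitted, in a model confined to the FPS-R or to self-reported numerical pain ratings. The same section should state whether pain scores from different scales are combined and, if so, how.

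The cost is one or two sentences and two degrees of freedom, which is negligible with about 83 evaluable participants (104 × 0.80 = 83.2). The Trial status section reports 103 participants already recruited, so this is a change to the analysis only and should be fixed before the outcome data are analysed.
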